## Analysis plan and samples sizes

1. Phase one: quantitative study

We will first perform descriptive statistical analyses of the answers to the web-questionnaires. We will then use a mixed model to describe clinicians’ perceptions of the attributes of the decision boxes (5-point smiley-faces rating scale, IAM), taking into account the clinical topic of the Decision Box, the study site, clinician’s status (nurse, resident, physician) and socio demographic characteristics of the participants. We will also perform multiple regression analyses to test relationships between clinicians’ intention to use what they learned from the Decision Boxand the determinants of their intention (attitude, subjective norm, perceived behavioral control), their status (nurse, resident, physician), their sociodemographic characterisitics (age, gender, number of years in practice), the study site, and the clinical topic of the Decision Box.

The regression analysis between clinicians’ intention and its determinants was used to set the needed sample size of clinicians. Earlier studies estimated regression coefficients of 0.78 for physicians
[18], and of 0.63 for nurses
[19] between intention and the three determinants of the intention (attitude, behavioral control and subjective norm). To be conservative, we used the lowest regression coefficient obtained for nurses (R^2^ = 0.63) to calculate the sample size, using two potential confounding variables (clinical topics and clinicians’ status). The ‘clinic’ effect was considered negligible as we have previously measured an Intraclass correlation coefficient of only 0.02 for clinicians nested within clinics in a cluster randomized controlled trial
[20]. Using these parameters we evaluated that a sample size of 78 clinicians gave a power of 90%. Based on a study of a continuing medical education program in shared decision-making where 70% of the physicians attended at least two of the three workshops
[21], we expect that about 70% of participating clinicians will complete at least half of the eight online questionnaires (1 questionnaire/Decision Box; 8 Decision Boxes). Consequently, to achieve a sample size of at least 78 clinicians who will complete at least four questionnaires, we need to recruit 111 clinicians (n = 5 clinics; 22 clinicians/clinic).

2. Phase 2: qualitative study

Two research professionals will independently perform a hybrid deductive/inductive thematic qualitative data analysis for each group and individual interview using specialized software (NVivo 9). Any disagreements will be discussed until consensus is reached. The coding scheme will be developed following the OMRU
[10,11], the Steps of the users' experience of an evidence-based shared decision-making support tool over time
[4], and the IP-SDM model
[14-16], by identifying what the PHT and the administrators of the primary care organizations experienced as barriers or facilitators to the application of what clinicians learned from the Decision Boxes. The deductive thematic analysis will apply attributes derived *a priori* from these theories and an inductive thematic analysis will integrate new themes, suggested by the data, into the scheme. We will compare the phenomena observed to emphasize a common tangent and will work out tree structures and matrices for the analysis. The first author (AG),will corroborate the findings by scrutinizing the analysis and ensuring that new themes, tree structures and matrices are representative of the initial data analysis and codes assigned.

We will combine data from phases one and two to identify the factors potentially influencing the implementation of the Decision Boxes in primary care. We will then tailor the implementation strategy to overcome the identified barriers and take into account the specific situation.

Approval of ethics for this project were given by the research ethics committee of the Centre de Recherche du Centre Hospitalier Universitaire de Quebec (reference number #S11-12-143), by the Research Ethic committee of the Jewish General Hospital in Montreal (reference number #12-014), and by the Research Ethics Board of McMaster University (reference number #11-550).

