### Data collection and procedures

1. Phase one: quantitative study

At study entry, all participating clinicians will sign an informed consent form and complete a questionnaire assessing their demographic and professional characteristics (age, gender, number of years of clinical practice). They will also rate their interest for each of the eight Decision Box topics using a visual analogue scale ranging from "no interest" to "great interest". Then, clinicians will receive the eight Decision Boxes by email, at a rate of one per week for eight weeks. For each Decision Box received, they will be prompted to complete a web-based questionnaire (Additional file
1). The first part of this questionnaire consists of a 5-point smiley-faces rating scale to assess global satisfaction with that Decision Box. The second part consists of questions based on the Theory of Planned Behavior (TPB)
[13] to study the characteristics of the clinicians that influence their intention to perform a given behavior. In this case, the behavior under study was ‘to use what I learned from the Decision Box to precisely explain the advantages and disadvantages of the options to my next patient to whom this intervention might apply’. Based on the TPB, the three determinants of a clinician’s intention to perform a behavior are: his/her attitude toward performing this behavior (perceived advantages and disadvantages of performing a behavior), his/her subjective norm (normative beliefs about the social pressure to engage or not to engage in this behavior), and his/her perceived behavioral control (beliefs, based on experience, about one’s ability to adopt this behavior). The third part of the questionnaire comprises the Information Assessment Method (IAM) that serves to evaluate cognitive impacts of the information, its relevance, usefulness and expected benefits
[12].

2. Phase 2: qualitative study

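### The intention analysis is named as multiple regression although each clinician reports intention up to eight times, so standard errors would be too small for some predictors and too large for clinical topic

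*Protocol article*

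**What the plan says.** Under Data collection and procedures, phase one, the article sets out repeated measurement: "For each Decision Box received, they will be prompted to complete a web-based questionnaire". The second part of that questionnaire holds the Theory of Planned Behavior (TPB) items, which cover intention, attitude, subjective norm and perceived behavioral control. With eight Boxes, a clinician can contribute up to eight intention scores.

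Under Analysis plan and samples sizes, phase one, two model types are named for the outcomes of this one questionnaire:

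- **Satisfaction scale and Information Assessment Method:** "We will then use a mixed model to describe clinicians’ perceptions of the attributes of the decision boxes".
- **Intention:** "We will also perform multiple regression analyses to test relationships between" intention and the three determinants, clinician status, age, gender and years in practice, together with "the study site, and the clinical topic of the Decision Box".

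The intention regression is also the analysis used to size the study. The only dependence discussed there is an "Intraclass correlation coefficient of only 0.02 for clinicians nested within clinics", which is treated as negligible. The target is counted in clinicians: "to achieve a sample size of at least 78 clinicians who will complete at least four questionnaires".

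**The concern.** Clinical topic is a covariate for intention, and it varies only between the Boxes that one clinician rates. Averaging to one row per clinician would largely remove it, so the rows must be clinician-by-Box questionnaires. Answers from the same clinician are likely to resemble each other, and multiple regression as named has no term for that. The clinic-level correlation of 0.02 concerns a different level and says nothing about it.

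The effect differs by predictor. Factors that are constant within a clinician (status, age, gender, years in practice) would be tested as if each questionnaire came from a different person. The TPB determinants share this problem as far as they correlate within clinician. Topic is a within-clinician comparison, so leaving between-clinician variation in the residual makes its standard error too large.

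Intention is the subject of specific question 2 in the Objectives. The identified barriers are to be used to tailor the intervention before a future RCT (Theoretical underpinnings). The Discussion singles out the influence of topic on intention as something this study is specially placed to examine. The named model therefore risks false-positive clinician factors and determinants, and lost power on topic.

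**Working it through.** **The plan's own figures.** 78/0.70 = 111.4; the article states 111, and 5 clinics × 22 = 110. This agrees within rounding. The 78 at 90% power could not be reproduced from R² = 0.63. Because the significance level and the tested hypothesis are not stated, 78 cannot be called wrong, and nothing below depends on its derivation.

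**Inputs from the article.** 78 clinicians; m = 4 to 8 questionnaires each (four is the planning threshold, eight the maximum), so 78 × 4 = 312 to 78 × 8 = 624 rows.

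**Assumptions (not in the article).** Residual within-clinician correlation ρ = 0.1, 0.3 or 0.5; within-clinician correlation of a TPB determinant ρx = 0.5; two-sided 5% tests.

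**Formulas.** The ratio of the true variance to the variance that the regression reports is

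- clinician-level factor: D = 1 + (m − 1)ρ
- determinant varying both between and within clinicians: D = 1 + (m − 1)ρxρ
- topic, balanced case: D = 1 − ρ

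True type I error = 2[1 − Φ(1.96/√D)].

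**Results.**

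| m | ρ | Clinician-level: D, error | Determinant (ρx = 0.5): D, error |
|---|---|---|---|
| 4 | 0.1 | 1.30, 8.6% | 1.15, 6.8% |
| 4 | 0.3 | 1.90, 15.5% | 1.45, 10.4% |
| 4 | 0.5 | 2.50, 21.5% | 1.75, 13.8% |
| 8 | 0.1 | 1.70, 13.3% | 1.35, 9.2% |
| 8 | 0.3 | 3.10, 26.6% | 2.05, 17.1% |
| 8 | 0.5 | 4.50, 35.6% | 2.75, 23.7% |

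For clinician-level factors the true standard error exceeds the reported one by a factor of √1.30 = 1.14 to √2.50 = 1.58 at m = 4, and √1.70 = 1.30 to √4.50 = 2.12 at m = 8.

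For topic, D = 0.9, 0.7, 0.5 gives a true standard error of 0.95, 0.84, 0.71 times the reported one, and a type I error of 3.9%, 1.9%, 0.6%.

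**Simulation check.** Ordinary regression on 78 clinicians with topic, one binary clinician-level factor and one determinant, no true effects, 2,000 data sets per setting:

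| m | ρ | Clinician-level | Determinant | Topic contrast |
|---|---|---|---|---|
| 4 | 0.1 | 8.9% | 6.4% | 4.0% |
| 4 | 0.3 | 15.2% | 10.6% | 3.6% |
| 4 | 0.5 | 22.1% | 13.9% | 2.7% |
| 8 | 0.1 | 12.8% | 8.6% | 3.9% |
| 8 | 0.3 | 27.8% | 18.7% | 1.8% |
| 8 | 0.5 | 34.8% | 22.7% | 1.0% |

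Simulation and formula agree for the first two columns. At m = 4 each simulated clinician rated a random four of the eight Boxes, so topic is partly a between-clinician comparison and its test is less conservative than the balanced formula suggests.

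**The case against.** **The article does not say that rows are treated as independent.** Multiple regression describes the covariate structure and does not by itself exclude a clinician effect or cluster-robust errors. A fuller plan may specify one, and counting the sample size in clinicians shows some awareness of the unit. This stands as a limit on certainty: the reading rests on the contrast with the preceding sentence, where a mixed model is named for the same questionnaire. It does not remove the point, because a model is named for intention and it is the wrong one for these rows.

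**A reader might infer that all p-values and intervals would be too optimistic.** The article does not support that. For topic, a stated interest, the error runs the other way.

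**The size is assumed.** This stands. No within-clinician correlation is given. What matters is the correlation left after the determinants are in the model, which could be lower or higher than that of intention itself.

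**The main result may survive.** If R² is near 0.63, about 11 to 26 observations would suffice for 90% power at a two-sided 5% level across the tests tried, and power at 78 is essentially 100%. The joint effect of the determinants would then probably hold even at one row per clinician. Tailoring also draws on the interviews of phase two. Both arguments lower the severity. They do not protect the individual determinants, the clinician-level factors or topic.

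**A reader might infer that clinicians with fewer than four questionnaires are excluded from the analysis.** The article uses four only as a threshold for planning recruitment and states no such exclusion.

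**Conclusion.** The point holds in a limited form. The article names multiple regression for an outcome measured up to eight times per clinician, includes a covariate that requires questionnaire-level rows, and considers clustering only at clinic level. Followed as written, the nominal 5% test would have a true type I error of about 9% to 36% for clinician-level factors, about 7% to 24% for TPB determinants, and about 4% down to 1% for topic.

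These ranges assume a residual within-clinician correlation of 0.1 to 0.5, a determinant correlation of 0.5 and 4 to 8 questionnaires per clinician. Even at 0.1 the test of a clinician-level factor runs at about 9% to 13%, so the direction does not depend on an extreme assumption, but no single figure can be given. The study is exploratory and its quantitative results are combined with qualitative ones, so this should be fixed before analysis but does not undermine the design.

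**What to change.** Replace the multiple regression for intention with a linear mixed model with a random intercept for clinician, keeping the covariates already listed and using every returned questionnaire. GEE or cluster-robust standard errors by clinician would be acceptable alternatives. Splitting each determinant into the clinician's mean and the deviation from it would separate differences between clinicians from differences between Boxes. That split is an optional modelling choice, and its absence is not an error.

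The cost is a change of wording in the analysis plan. The model class is already planned for the perception outcomes, and no further data or recruitment are needed. Confidence intervals for clinician-level factors will be wider, as will those for the determinants as far as they correlate within clinician; those for topic should be narrower.

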## Discussion

This project aims to study the factors that influence the use of a novel tool to facilitate SDM by primary healthcare teams. Factors related to the innovation itself, the potential users, and the context of use will be assessed.

Delivery of this tool in naturalistic settings will allow assessment of contextual barriers to uptake, and will help collect realistic perceptions on the value of the tool. Because eight Decision Boxes on various topics will be delivered, this project also represents a unique opportunity to explore the influence of the clinical topic on clinicians’ intention to use what they learned from the Decision Boxto explain the advantages and disadvantages of the options to their patients. The Decision Boxes will be written in both the official languages of Canada, French and English, allowing a wider dissemination in the country. As the study will include professionals from three cities located across two provinces in Canada, results will then also be generalizable to a wider population. However, the clinicians we will recruit may not be representative of all practicing physicians in the targeted settings - only those interested in Evidence-Based Medicine and/or SDM are likely to accept participating.

The Decision Box is a new tool available to clinicians who decide to use SDM to make a decision with their patient. A review of interventions to improve health professionals’ adoption of SDM in clinical practice suggest that, both patient-mediated interventions, such as Patient Decision Aids, and training of health professionals are important to the successful implementation of SDM in clinical practice
[22]. As a self-directed learning approach, the Decision Box may complement group learning activities already available to teach shared decision-making
[23].

Additional benefits of this project include the development of a website hosting the Decision Boxes, further facilitating access for clinicians, researchers, and patients.

This project will allow tailoring of Decision Boxes and their delivery to overcome the specific barriers for change identified in primary care clinicsin Canada. By helping implement Decision Boxes in clinical practice, this study may potentially enhance the transfer of scientific data to healthcare professionals, and also improve communication between healthcare professionals and patients, thus allowing a more judicious use of the current best available evidence in clinical decision making.

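### The one intention regression described adjusts clinical topic for attitude, subjective norm and perceived control, so its topic coefficient is a direct effect and can understate topic's overall influence on intention

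*Protocol article*

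**What the plan says.** The protocol article, Analysis plan and samples sizes, phase one, sets out three steps.

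- Descriptive analyses of the questionnaire answers.
- A mixed model: "We will then use a mixed model to describe" perceptions of the boxes. Its outcomes are the satisfaction scale and the Information Assessment Method. It includes topic, site, status and sociodemographics.
- For intention: "We will also perform multiple regression analyses to test relationships between" intention and a list of terms. The list runs from "the determinants of their intention (attitude, subjective norm, perceived behavioral control), their status (nurse, resident, physician") through age, gender and years in practice to "the study site, and the clinical topic of the Decision Box".

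The sample-size paragraph of the same section describes the regression of intention on its determinants as "using two potential confounding variables (clinical topics and" clinicians' status), which gives topic and status the role of adjustment variables.

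Data collection and procedures states the theory: "Based on the TPB, the three determinants of a clinician’s intention to perform a behavior are" attitude, subjective norm and perceived behavioral control. The same section says that clinicians are prompted to answer the questionnaire for each box they receive.

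The Discussion adds an aim for topic: "this project also represents a unique opportunity to explore the influence of the clinical topic on clinicians’ intention".

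**The concern.** Attitude, norm and control are not baseline characteristics here. They are answered box by box, about using what that box taught, so topic comes before them and may shift them. Status and site also precede them. Under the TPB as the article adopts it, these constructs are the determinants of intention, so a topic that makes clinicians more or less inclined to use a box could plausibly do so largely by changing them.

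A regression holding the constructs fixed removes that part of topic's effect. What remains answers a narrower question: does topic matter among clinicians with the same attitude, norm and control? A small or null coefficient could then be reported as showing that topic has little influence on intention, although intention differs clearly between topics. Theoretical underpinnings and the Discussion say the findings will be used to tailor the boxes and their delivery, so the misreading could carry over into that work.

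**Working it through.** The article gives no figure for topic's effect on intention, so there is none to reproduce. The check has three parts.

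**1. Which model is described.** Topic, status and site stand in one list with the three constructs, and topic and status are called confounders of the determinant-intention relation. Confounders are normally entered alongside the exposure, so a joint model is the natural reading. The only other model containing topic has different outcomes. No regression of intention without the constructs, no order of entry and no mediation analysis is described.

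**2. What the joint coefficient estimates.** In a linear model, let a_j be the topic contrast on construct j, b_j that construct's coefficient for intention, and d the direct topic contrast.

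- Total contrast = d + Σ a_j b_j
- Topic coefficient in the joint model = d
- With mediated share s = Σ a_j b_j / total, joint coefficient = (1 − s) × total

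As an assumed example, let a topic lower attitude by 0.5 SD, with an attitude coefficient of 0.6 and no other path. The total is −0.5 × 0.6 = −0.30 SD and the joint coefficient has expectation 0. For a total of −0.30 SD, across the range of s:

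| Mediated share s | Joint coefficient (SD) |
|---|---|
| 0 | −0.30 |
| 0.25 | −0.225 |
| 0.50 | −0.15 |
| 0.75 | −0.075 |
| 1 | 0 |

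**3. Simulation at the planned size.** The article supplies the dimensions: 78 clinicians, four questionnaires each, eight topics. All effects are assumed. The highest-versus-lowest topic contrast on each construct is 1.0, and the construct coefficients are 0.4, 0.3 and 0.3, so the mediated contrast is 1.0 × (0.4 + 0.3 + 0.3) = 1.00. The constructs explain about 70 to 73% of the variance in intention. Least-squares fits with and without the constructs, 500 runs per row, topic tested at 5%:

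| Direct contrast d | Without constructs | Joint model | Topic test rejects, without | Topic test rejects, joint |
|---|---|---|---|---|
| 0 | 1.00 | 0.01 | 100% | 3% |
| 0.2 | 1.20 | 0.20 | 100% | 33% |
| 0.4 | 1.40 | 0.40 | 100% | 95% |
| 0.8 | 1.79 | 0.80 | 100% | 100% |

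In every row the joint model returns the direct part and nothing more, as the formula says. The contrasts show the mechanism. They do not predict this study's results.

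**The case against.** The strongest reply is that the regression is built for another question. The abstract gives its purpose as studying the determinants of intention, and the sample size was set on that relation. For the determinants' coefficients, adjusting for topic, status and site is appropriate. This stands, and the joint model should stay. Whether topic adds anything beyond the constructs is also a legitimate question, and the joint model answers it.

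A reader might infer that the study has only one intention model and cannot show topic's influence at all. The article does not support that. It speaks of analyses in the plural and fixes no order of entry. The joint model shows the direct part. All clinicians are to receive all eight boxes, so a descriptive breakdown of intention by topic would approximate the overall contrast apart from selective non-completion. However, the article does not commit to such a breakdown, and it would not adjust for which clinicians answered which boxes.

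Nor do the documents support a claim that the topic coefficient will be near zero. That topic, status or site acts through the three constructs is inferred from the TPB and is not stated.

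The aim is also modest. Topic's effect on intention is not among the three specific questions under Objectives and appears only in the Discussion, as something to explore. No aim of estimating the overall effect of status or site is stated. Tailoring will draw on interviews and on the satisfaction and Information Assessment Method models as well, so it does not rest on this coefficient alone.

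Finally, a condensed article may leave model-building detail to a fuller document. That excuses the missing order of entry. It does not remove the mismatch between the variable list that is stated and the aim that is stated.

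**Conclusion.** The point holds in a limited form. The only intention regression described lists topic with constructs that are measured after it and may carry part or most of its effect. Read as a joint model, it gives a residual direct effect for topic, and likewise for status and site. That does not answer the Discussion's question about topic's influence on intention and can understate it.

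The understatement is the mediated share s, which may lie anywhere from none to all of the effect and which the documents do not give. This rests on three assumptions: the listed terms enter together, topic affects at least one construct, and the direct and mediated parts have the same sign. If their signs differed, the joint coefficient would still not be the overall effect, but it need not be smaller.

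The determinants' own coefficients are not called into question. For status and site, the point concerns only how their coefficients are read.

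**What to change.** - Keep the joint model as listed, and use it for the coefficients of attitude, subjective norm and perceived behavioral control.
- Add a regression of intention on topic, status, site and sociodemographics without the three constructs, treating repeated ratings from the same clinician as in the joint model. Report topic's overall association with intention from it.
- Label the topic, status and site coefficients of the joint model as direct effects, given the three constructs. State that a null value there does not show that topic, status or site is unrelated to intention.

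The cost is one extra model and a few sentences in the analysis section. No new data, participants or questionnaire items are needed.

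### The stated inputs do not yield 78 clinicians at 90% power, and 0.63 is called both a regression coefficient and R-squared, so the effect that has 90% power is unidentified

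*Protocol article*

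**What the plan says.** Everything is in the protocol article, section Analysis plan and samples sizes, under Phase one.

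- Basis: "The regression analysis between clinicians’ intention and its determinants was used to set the needed sample size of clinicians".
- Source of the effect size: "Earlier studies estimated regression coefficients of 0.78 for physicians" and 0.63 for nurses, each described as holding "between intention and the three determinants of the intention (attitude, behavioral control and subjective norm").
- Value used: "we used the lowest regression coefficient obtained for nurses (R^2^ = 0.63) to calculate the sample size".
- Covariates: "using two potential confounding variables (clinical topics and clinicians’ status").
- Clinic: treated as negligible, citing an intraclass correlation of 0.02.
- Result: "Using these parameters we evaluated that a sample size of 78 clinicians gave a power of 90" per cent.

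The 78 is then divided by an expected 70% completion to give a recruitment target of 111. The regression planned in the same section carries the three determinants, status, age, gender, years in practice, study site and clinical topic.

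**The concern.** The result is presented as following from the listed parameters. An R-squared of 0.63 is a very strong relationship, and a test of whether three predictors explain that much variance needs few observations. Seventy-eight looked several times too large for it. That suggests the calculation addressed a different and smaller effect, which the text does not name.

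The key input also has two labels in one phrase. A regression coefficient, a multiple correlation and R-squared are different quantities. With 0.63 as R-squared the residual variance is 0.37; with 0.63 as a multiple correlation it is about 0.60.

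This is the only power statement in the article, and it sets recruitment. The article says that the barriers identified will be used to tailor the intervention before a later randomised trial. Readers should therefore be able to tell which relationships the regression had 90% power to detect.

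**Working it through.** **Inputs from the article:** 0.63; three determinants; two confounders (topic with eight levels, status with three); clinic effect ignored; N = 78; power 90%.

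**Assumption:** two-sided alpha 0.05, which the article does not state.

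**Method:** noncentral F test in multiple regression. The effect size is f² = (R-squared attributed to the tested terms) / (1 − full-model R-squared), the noncentrality is N × f², there are u tested degrees of freedom, and the error df are N − p − 1 with p predictors.

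**Step 1: the article's figure, 0.63 read as R-squared.** f² = 0.63 / 0.37 = 1.703. At N = 78 the noncentrality is 78 × 1.703 = 132.8. As in the article, the whole 0.63 is attributed to the tested terms.

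| Test | u | p | N for 90% power | Power at 78 |
|---|---|---|---|---|
| Determinants jointly, confounders as 2 df | 3 | 5 | 14 | >99.99% |
| Determinants jointly, confounders as 7 + 2 df | 3 | 12 | 19 | >99.99% |
| Overall test, 5 predictors | 5 | 5 | 17 | >99.99% |
| Overall test, 12 predictors | 12 | 12 | 26 | >99.99% |
| Overall test, all planned terms | 19 | 19 | 34 | >99.99% |

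The 19 df are 3 determinants + 7 topic + 2 status + 4 site + age, gender and years in practice. The figure of 78 is not reproduced.

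**Step 2: 0.63 read as a multiple correlation.** R-squared = 0.63² = 0.397, f² = 0.397 / 0.603 = 0.658, and the noncentrality at 78 is 51.3. The joint test needs 26 (determinants alone), 27 (2 covariate df) or 29 (9 covariate df). The overall test needs 32, 45 or 56 (5, 12 or 19 df). Power at 78 is above 99% in each case; the lowest is 99.2%, for the 19-df test. Again 78 is not reproduced.

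**Step 3: sensitivity to alpha.** At alpha 0.01, for tests with up to 12 df, the largest N is 32 (0.63 as R-squared) or 58 (0.63 as a correlation). A stricter conventional alpha does not explain 78.

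**Step 4: what does 78 at 90% correspond to?** Solving for f² at N = 78, power 90% and alpha 0.05:

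- 1-df test: f² ≈ 0.138. At full-model R-squared 0.63, the gain is 0.138 × 0.37 = 0.051.
- 3-df test: f² ≈ 0.192. At full-model R-squared 0.63, the gain is 0.192 × 0.37 = 0.071.
- A 3-df gain of 0.06 on top of a base R-squared of 0.63 also works: f² = 0.06 / (0.37 − 0.06) = 0.194, which gives N = 78.

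Several different effects thus lead to 78 or close to it. The article states none of them, so the one intended cannot be recovered from the text.

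**Step 5: does the number of covariates matter?** For a 1-df gain of 0.051 at full-model R-squared 0.63, power at 78 is 0.899 with 5 predictors, 0.898 with 12 and 0.897 with 19. The extra terms in the planned model cost about 0.2 percentage points.

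**The case against.** **A condensed article may omit detail.** Leaving out alpha or software settings would be no finding on its own. The point here is that the article says its listed parameters give 78, and they do not, and that it labels one number in two ways.

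**The label is only loose wording.** This has force. Where the number is used it is marked as R-squared, and a single value linking intention to three determinants cannot be one slope. Whether the source reports R or R-squared cannot be settled from the article, so the correlation reading is a conditional check. The mismatch does not depend on it.

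**If anything, 78 is generous.** This stands for the joint and overall tests. A reader might infer from the unexplained figure that the study is underpowered and would miss a real determinant. The article does not support that. Low power appears only if one supposes a particular small gain in R-squared, and the article states none. Nor does one back-calculated gain prove what the authors intended, since both 1-df and 3-df gains lead to about 78.

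**The units and the model size.** The calculation counts clinicians, yet it adjusts for topic, which varies between questionnaires of the same clinician. With 78 clinicians completing at least four questionnaires each, the regression would have at least 78 × 4 = 312 records, so counting each clinician once does not overstate the information. This should be stated openly, but no loss of power has been shown. The gap between two confounders and the full model is numerically immaterial (step 5).

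**Conclusion.** The power statement is wrong as written: the stated inputs lead to about 14 to 19 clinicians for the joint test of the determinants, or 17 to 34 for an overall test, against the 78 reported. On the joint-test reading the gap is about four- to more than five-fold (78 / 19 = 4.1; 78 / 14 = 5.6). Power at 78 exceeds 99.99% with 0.63 as R-squared and 99% with 0.63 as a multiple correlation. These results assume alpha 0.05 and an ordinary fixed-effects regression with one record per clinician.

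What follows is limited: the 90% cannot be verified and the effect it belongs to is not identified. It does not follow that 78 is too few or that recruitment of 111 should change.

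**What to change.** Keep 78 and rewrite the power sentence so that it:

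- says, after checking the cited sources, whether 0.63 is R or R-squared, and uses that one label throughout;
- names the test that was powered (three determinants jointly, or one determinant), its degrees of freedom, alpha and the gain in R-squared assumed;
- gives the power, or the smallest detectable gain, that 78 clinicians deliver for that test;
- states that the calculation counts each clinician once, although the regression uses repeated questionnaires per clinician.

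The authors should take the assumed gain from their own calculation; the values in step 4 show only what is compatible with 78. The cost is one paragraph and a short recalculation, with no extra clinicians. The stated power figure may change.
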